## Abstract

**Background:**

Transcranial temporal interference stimulation (tTIS) is a new, emerging neurostimulation technology that utilizes two or more electric fields at specific frequencies to modulate the oscillations of neurons at a desired spatial location in the brain. The physics of tTIS offers the advantage of modulating deep brain structures in a non-invasive fashion and with minimal stimulation of the overlying cortex outside of a selected target. As such, tTIS can be effectively employed in the context of therapeutics for the psychiatric disease of disrupted brain connectivity, such as major depressive disorder (MDD). The subgenual anterior cingulate cortex (sgACC), a key brain center that regulates human emotions and influences negative emotional states, is a plausible target for tTIS in MDD based on reports of its successful neuromodulation with invasive deep brain stimulation.

**Methods:**

This pilot, single-site, double-blind, randomized, sham-controlled interventional clinical trial will be conducted at St. Michael’s Hospital **–** Unity Health Toronto in Toronto, ON, Canada. The primary objective is to demonstrate target engagement of the sgACC with 130 Hz tTIS using resting-state magnetic resonance imaging (MRI) techniques. The secondary objective is to estimate the therapeutic potential of tTIS for MDD by evaluating the change in clinical characteristics of participants and electrophysiological outcomes and providing feasibility and tolerability estimates for a large-scale efficacy trial. Thirty participants (18–65 years) with unipolar, non-psychotic MDD will be recruited and randomized to receive 10 sessions of 130 Hz tTIS or sham stimulation (*n* = 15 per arm). The trial includes a pre- vs. post-treatment 3T MRI scan of the brain, clinical evaluation, and electroencephalography (EEG) acquisition at rest and during the auditory mismatch negativity (MMN) paradigm.

**Discussion:**

This study is one of the first-ever clinical trials among patients with psychiatric disorders examining the therapeutic potential of repetitive tTIS and its neurobiological mechanisms. Data obtained from this trial will be used to optimize the tTIS approach and design a large-scale efficacy trial. Research in this area has the potential to provide a novel treatment option for individuals with MDD and circuitry-related disorders and may contribute to the process of obtaining regulatory approval for therapeutic applications of tTIS.

**Clinical Trial Registration:**

ClinicalTrials.gov, identifier NCT05295888.

## 1 Introduction

Major depressive disorder (MDD) is a prevalent and debilitating mental illness with a substantial health and economic burden (Lam et al., 2016). Approximately 280 million people in the world, or 5% of all adults, suffer from MDD (Institute of Health Metrics and Evaluation, 2019). Its clinical manifestations are characterized by major depressive episodes (MDEs) – periods of persistently low mood and anhedonia typically lasting for at least 2 weeks at a time. More than 30% of individuals with MDD receiving adequate dose and duration of pharmacotherapy become treatment-resistant, and of those who do respond to treatment, over 65% never reach remission (Rush et al., 2006). Similarly, only 25% of treatment-resistant individuals receiving intensive psychotherapy reach remission (Schatzberg et al., 2005), and capacities in such programs are often insufficient to meet the demand. The magnitude of the MDD burden largely reflects the limited effectiveness of available treatment. Given the critical nature of the illness, with cases often involving suicidal ideation and a lack of an optimal therapeutic outcome (i.e., remission), there is an urgent need for more effective, scalable treatment strategies.

### 1.1 Brain stimulation: the need for optimal targeting

Antidepressants are considered to be the first-line treatment for moderate-to-severe MDD (Anderson et al., 2008). However, many individuals do not respond to these medications and meet the criteria for treatment-resistant depression (TRD); thus, alternative therapeutic options have been explored. In particular, brain stimulation techniques have been used in cases where first-line therapy has not been effective or feasible. One well-established, effective non-invasive brain stimulation (NIBS) technique that is approved by the United States Food and Drug Administration (FDA) for the treatment of severe depression is electroconvulsive therapy (ECT). However, this technique requires anesthesia and seizure induction. As such, some individuals may be apprehensive about undergoing ECT due to its potential side effects, such as memory loss, as well as the associated stigma and a lack of understanding of the ECT procedure itself. Deep brain stimulation (DBS), which is FDA-approved for movement disorders such as Parkinson’s disease and essential tremor, as well as dystonia, epilepsy, and obsessive-compulsive disorder, has also shown promise in treating depression, specifically TRD, although clinical trials have produced mixed results (Hitti et al., 2020; Figee et al., 2022). Irrespective of its potential efficacy, DBS is an invasive procedure that can lead to surgical complications and adverse effects, making it suboptimal to a substantial number of treatment candidates (Boviatsis et al., 2010; Fenoy and Simpson, 2014; Moro, 2016). Furthermore, the administration of DBS requires personnel with a high degree of specialization, which limits its accessibility. These factors warrant the investigation of effective brain stimulation techniques that would overcome these limitations.

Recently, several other NIBS techniques have received increased attention in depression research, as they may overcome the aforementioned limitations of ECT and DBS while achieving comparable therapeutic effects. Some notable examples include transcranial electrical stimulation (TES) and transcranial magnetic stimulation (TMS), the latter of which is FDA-approved for the treatment of TRD. Through the modulation of neuroplasticity, these NIBS modalities induce long-lasting changes in the excitability of brain regions involved in regulating thoughts, emotions, and behavior (Boes et al., 2018; Polanía et al., 2018). The therapeutic potential of NIBS stems from its ability to evoke immediate and sustained directional modulation of neural network activity in either an excitatory or inhibitory fashion (Miniussi et al., 2013; Cantone et al., 2017) or by modifying the threshold of synaptic plasticity (Karabanov et al., 2015; Hassanzahraee et al., 2018). Several meta-analyses and systematic reviews have demonstrated the efficacy and tolerability of both TES and TMS for the treatment of depression (Berlim et al., 2014; Kedzior et al., 2014; Dunlop et al., 2017; Pacheco et al., 2021). Furthermore, response and remission rates for these modalities remain in the range of 33%–45% and 16%–22%, respectively (Cao et al., 2018; Razza et al., 2020), although individual studies have shown much higher remission rates, such as with transcranial alternating current stimulation (tACS) in MDD (54% remission) (Wang et al., 2022) or the Stanford Accelerated Intelligent Neuromodulation Therapy (SAINT) protocol for neuronavigated intermittent theta-burst repetitive TMS in TRD (57%–86% remission) (Cole et al., 2020, 2022).

Safety and tolerability are considered to be relative advantages of NIBS, as risks and adverse events have been well studied over the past 25 years and are reflected in international consensus safety guidelines (Nitsche et al., 2003; Poreisz et al., 2007; Rossi et al., 2009). However, when deployed with the aim of inducing excitability changes in deeper brain structures, such as the limbic areas or basal ganglia, most NIBS techniques, including TES and TMS, are unable to reach these structures without inadvertently co-stimulating more superficial brain tissue. Due to the physical properties of applied electric current or magnetic field, focality decreases with increasing depth, and neuromodulation of deeper brain tissue is achieved at the expense of applying stronger stimulation of the overlying cortex, which, aside from non-specific targeting alone, may lead to adverse effects and a breach of safety guidelines (Deng et al., 2013). Due to this depth/focality trade-off, TMS and TES are limited to the stimulation of relatively superficial cortical regions.

Given these issues, much excitement has surrounded a major new technological development in the world of NIBS – second-generation brain stimulation techniques that rely on acoustic, optical, magnetic, and electric signals (Liu et al., 2022). These include focused ultrasound, near-infrared optogenetic, and nanomaterial-enabled magnetic stimulation, all of which offer great prospects for neuromodulation. Another technique is transcranial temporal interference stimulation (tTIS) – a form of tACS that uses combinations of spatially interacting electric fields to target deep brain structures with markedly reduced stimulation of the overlying cortex (Grossman et al., 2017, 2018). The translational potential of tTIS to provide improved treatment for neurological and psychiatric disorders follows its purported neuromodulatory mechanisms that are similar to other brain stimulation techniques but with two distinct advantages – non-invasiveness, as opposed to DBS, and spatial accuracy, as opposed to TES and TMS (Lozano, 2017; Grossman et al., 2018).

### 1.2 Transcranial temporal interference stimulation

While the literature on tACS in depression research is nascent in comparison to TMS, tACS serves as a promising NIBS technique with high therapeutic potential and minimal side effects, with clinical trials for MDD already emerging (Alexander et al., 2019; Wilkening et al., 2019; Haller et al., 2020; Riddle et al., 2022). However, the electric fields induced by conventional tACS are fairly broad (Datta et al., 2009; Rampersad et al., 2014), making it difficult to target specific brain regions with high focality. Moreover, electric fields applied with tACS dissipate with the traveled distance, so the stimulation of desired deep brain structures unavoidably results in unwarranted co-stimulation of the overlying cortex.

When applied at a frequency that corresponds to the frequency range of endogenous neural oscillations (0.1–80 Hz) and in the so-called “ripple range” (140 Hz) (Moliadze et al., 2010), tACS may be able to interact with ongoing rhythms in the cortex by synchronizing them with the applied tACS current sine wave, which itself acts as an exogenous oscillation. When applied in the low kHz range (1–5 kHz), tACS is able to selectively target the membrane excitability of neurons by altering the accumulation of calcium in the presynaptic nerve terminals (Citri and Malenka, 2008), but this kHz range does not entrain with or synchronize neuronal oscillatory activity due to the low-pass filtering properties of the neuronal cell membrane (Antal and Paulus, 2013). On the other hand, tTIS involves the simultaneous application of two or more independent sinusoidally oscillating current waveforms at slightly different high frequencies, which alone do not influence neuronal activity due to the neuronal membrane’s low-pass filter (Grossman et al., 2017, 2018; Lozano, 2017). The combination of two high-frequency sine waves of slightly different frequencies (e.g., 1,000 and 1,130 Hz), however, generates two electric fields that overlap and form a high-frequency carrier wave (the average of the two input frequencies, 1,065 Hz) that is modulated by a low-frequency envelope oscillating at the much lower “beat” frequency that represents the absolute difference of the two sinusoids (e.g., 130 Hz). tTIS effects depend on this “beat” interaction to drive neuromodulation. Since the strength of the stimulation at any given location is determined by the electric field that is lower in amplitude, the resulting focus is much smaller and enables better targeting. Mechanistically and much like for conventional tACS, it has been shown that tTIS alters the timing, but not the rate, of neuronal spiking activity, with the exception that tTIS offers a way to disrupt pathological oscillatory activity focally and reduce neural synchrony in deep brain structures (Vieira et al., 2024).

This concept was formed and validated by Grossman et al. (2017) using rodent models (Grossman et al., 2017). They performed two experiments with the aim of stimulating the mouse hippocampus through the surface of the skull. The first experiment delivered direct 10 Hz stimulation, and the second experiment delivered 2,000 and 2,010 Hz currents to achieve a “beat” frequency of 10 Hz. With the 10 Hz current, both the hippocampus and cortex were engaged, as indicated by the presence of *c-fos* expression, whereas with the tTIS “beat” frequency of 10 Hz, only the hippocampus was activated. Furthermore, finite element modeling of simulations of tTIS electric fields in human anatomical models suggests that large deep brain structures, such as the hippocampus or subgenual anterior cingulate cortex (sgACC), could also be selectively targeted (Grossman et al., 2017, 2018; Rampersad et al., 2019).

For the past 70 years, temporal interference stimulation (TIS) has been employed in research, typically under the name of *interferential current therapy*, as an effective supplemental tool for physical rehabilitation by electrically stimulating deep muscle tissue (Goats, 1990; Fuentes et al., 2010). More recently, TIS has been used as a neurorehabilitation tool, particularly in the treatment of Parkinson’s disease, Alzheimer’s disease, stroke, and aphasia (Brown, 1975; Goats, 1990; Fuentes et al., 2010; Moore et al., 2018; Skipper et al., 2018; Hussein et al., 2022). The safety profile of TIS has been demonstrated in several preclinical studies, indicating that it does not induce DNA damage, changes in synaptic density, or changes in tissue temperature, nor does it alter the intensity and density of immunohistochemically stained neurons (Grossman et al., 2017; Esmaeilpour et al., 2021; Missey et al., 2021; Sunshine et al., 2021). Modifications to the physics of TIS have also been actively explored. For instance, square electric fields creating a pulse-width modulated interfering electric field have been shown to stimulate neuronal activity as effectively as conventional tTIS with sinusoidal electric fields (Luff et al., 2024). Moreover, the introduction of a phase-canceling electric field appears to improve the focality of tTIS and reduce off-target stimulation (Savvateev et al., 2023).

Several studies have also shown the successful use of tTIS in humans. Devaney et al. (2020) were the first to demonstrate tTIS safety in the human visual cortex using a “beat” frequency of 10 Hz, which was well tolerated in the entire sample and resulted in no disturbances in visual perception (Devaney et al., 2020). Several studies followed suit and demonstrated the feasibility, safety, and functional engagement of stimulated targets with tTIS in healthy humans (Wessel et al., 2021; Ma et al., 2022; Piao et al., 2022; von Conta et al., 2022; Zhang et al., 2022; Zhu et al., 2022); most of these studies, however, aimed to engage superficial primary cortices as targets where other NIBS modalities, such as TES or TMS, are already capable of inducing neuromodulation. Three more recent studies successfully showed the engagement of deep brain structures in healthy humans with tTIS, notably the hippocampus (Violante et al., 2023) and striatum (Wessel et al., 2023; Vassiliadis et al., 2024a). In these studies, target engagement was confirmed through independent evaluation of task-based functional magnetic resonance imaging (fMRI) and a behavioral experiment, and these results lay the groundwork for designing a subsequent round of human tTIS studies with alternative targets. Notably, the work by Vassiliadis et al. (2024a) showed that tTIS was able to selectively modulate striatal mechanisms involved in motor reinforcement learning in humans, using tTIS as a tool to highlight the causal relationship between the function of this deep brain structure and human behavior. In regard to the feasibility of deep tTIS in humans, findings from 119 human participants and >250 stimulation sessions support its safety and tolerability profile and ascertain its excellent blinding efficiency for sham-controlled designs (Vassiliadis et al., 2024b).

Taken together, tTIS offers a novel opportunity over tACS in terms of targeting accuracy and specificity. First, because the tTIS field at its beat frequency, which is considered the component that may result in neuromodulation, can reach deep brain structures with higher field strengths than in the overlying areas. Second, because this field has a smaller focus than regular tACS for deep as well as superficial brain regions.

### 1.3 Therapeutic target: subgenual anterior cingulate cortex

As the first clinical trial to evaluate the prospects of tTIS for MDD, we selected the sgACC [Brodmann Area 25 (BA25)] as our target of interest based on its likely role in MDD symptomatology and treatment response, as well as its rich connectivity profile (Mayberg, 2009). Antidepressant response to active and placebo pharmacotherapy, cognitive-behavioral therapy (CBT), and ECT manifests itself in target engagement of the sgACC (Mayberg et al., 1999; Chen et al., 2007; Mayberg, 2009), and functional hyperactivity of this region best characterizes more treatment-resistant patients (Seminowicz et al., 2004; Mayberg et al., 2005; Greicius et al., 2007). Importantly, high-frequency (>100 Hz) DBS of the sgACC, which mimics the stimulation effects of tTIS proposed in this clinical trial protocol, leads to a long-term response and remission in TRD cohorts (Holtzheimer et al., 2017; Sobstyl et al., 2022). Depressed patient samples are characterized by anatomical sgACC changes on structural MRI scans as well as post-mortem identified glial cell abnormalities (Drevets et al., 1997; Öngür et al., 1998). Moreover, structural and functional variability in this region has been linked to a normal polymorphism in the serotonin transporter, an emerging risk factor for depression (Pezawas et al., 2005). Overall, converging anatomical and histological findings complement broad functional imaging literature, which links sgACC activity to the regulation of negative emotional states. This has been illustrated by sgACC hyperactivity observed in response to provoking sad mood through tryptophan depletion (Ghashghaei et al., 2007), passive exposure to emotionally charged stimuli (Zald et al., 2002; Siegle et al., 2006), and autobiographical memories (Mayberg et al., 1999).

The basis of a more specific role of the sgACC in MDD is grounded in abundant afferent and efferent connections between the sgACC and the insula, brainstem, and hypothalamus, evident in autonomic and circadian components of emotion regulation, including stress response, as well as alterations in sexual functioning, sleep, appetite, neuroendocrine, and neuroimmune functioning (Freedman et al., 2000; Vertes, 2004; Ghashghaei et al., 2007; Hsu and Price, 2007). Reciprocal pathways linking the sgACC BA25 to orbitofrontal, medial frontal, and dorsal prefrontal cortices, the anterior and posterior cingulate cortices, and the amygdala, hippocampus, and nucleus accumbens further identify plausible pathways through which interceptive and homeostatic processes might influence aspects of learning, memory, reward, and reinforcement (Haber et al., 2006; Petrides and Pandya, 2007), which are the core cognitive and behavioral components impaired in depressed individuals. These structural and functional connections display considerable overlap with patterns of regional changes observed in response to pharmacotherapy and CBT, providing a solid foundation to pursue strategies that might effectively alter the sgACC connectivity in individuals with MDD rather than focusing on merely normalizing the absolute activity of the sgACC in isolation. The repeated observations of cellular abnormalities in the sgACC of depressed patients post-mortem, studies of acute emotional states, and predictable decrease in the sgACC activity in response to pharmacological and somatic antidepressant treatments provide a solid foundation to test the therapeutic potential of direct modulation of the sgACC (BA25) using high-frequency tTIS as a novel intervention strategy.

## 2 Objectives and hypotheses

The overarching goal of this study is to continue establishing the prospects of tTIS in humans and provide novel evidence for the impact of tTIS on metrics of the sgACC target engagement across several neuroimaging modalities. This study also intends to establish the feasibility, tolerability, and therapeutic potential of repetitive tTIS for MDD, thus pioneering the investigation of a course of tTIS sessions in a clinical population. Furthermore, it will attempt to establish a causal relationship between the manipulation of the sgACC with tTIS and changes in its target engagement metrics during the resting state, as well as electrophysiological and clinical correlates of depressive symptoms.

Our primary aim is to demonstrate target engagement of the sgACC with tTIS in participants with MDD using the resting-state fMRI, arterial spin labeling (ASL), and diffusion-weighted MRI, as evidenced by pre- vs. post-treatment changes in its intrinsic activity, functional connectivity (FC), perfusion, and anatomical connectivity with other brain regions. We hypothesize that in participants with MDD, a course of 10-day active 130 Hz tTIS will induce engagement of the sgACC post-treatment, which will be superior to sham. Target engagement will be measured as pre- vs. post-treatment change in: (a) resting-state blood-oxygen-level-dependant (BOLD) activity, quantified by power in the BOLD characteristic frequency range (0.015–0.08 Hz), (b) perfusion metrics of cerebral blood flow (CBF), and (c) BOLD activity and CBF in resting-state functional and anatomical networks, or brain regions that are strongly coherent with the sgACC functionally and connected anatomically. We hypothesize that we will observe (a) an increase in BOLD activity in sgACC voxels in tTIS arms but not the sham due to the direct stimulation of the area, (b) an increase in CBF in sgACC voxels in tTIS arm but not the sham due to the direction stimulation of the area, (c) an increase in FC between sgACC and dorsolateral prefrontal cortex (dlPFC), ventromedial prefrontal cortex (vmPFC), and insula – the nodes that display reduced baseline resting-state FC in unmedicated MDD patients compared to healthy controls (Murrough et al., 2016; Wang et al., 2018; Cheng et al., 2021), (d) a significant association between changes in the FC of the sgACC with the abovementioned nodes and anatomical connectivity. Our secondary aim is to demonstrate, using a randomized sham-controlled design, the feasibility, tolerability, and therapeutic potential of repetitive tTIS in participants with MDD. We hypothesize that a 10-day active 130 Hz tTIS will produce significantly greater improvement than sham stimulation in scores of standardized clinical measures of mood symptoms severity in MDD, anxiety, quality of life, and functional impairment. We will also perform exploratory analyses of (a) pre- vs. post-stimulation changes in whole-brain resting-state FC of the sgACC, (b) pre- vs. post-stimulation changes in resting-state electroencephalography (EEG) spectral power after a single session of tTIS and over the course of 10 sessions, (c) pre- vs. post-stimulation changes in the amplitude and latency of the auditory mismatch negativity (MMN) event-related potentials (N1 and P1) after a single session of tTIS and over the course of 10 sessions, (d) feasibility of performing concurrent EEG acquisition during tTIS (termed tTIS-EEG), and (e) source signal propagation during concurrent tTIS-EEG using our proposed configuration for the stimulation of the sgACC with tTIS.

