### 3.12 Analysis plan

#### 3.12.1 Primary outcomes: target engagement

BOLD activation (power in the 0.015–0.08 Hz frequency range), CBF, seed-based resting-state FC, and anatomical connectivity of the sgACC will be the primary outcome measures to demonstrate sgACC target engagement with a course of tTIS. We hypothesize that we will observe an increase in the BOLD activation and CBF in the sgACC voxels in the tTIS arm but not the sham and an increase in resting-state FC between the sgACC and bilateral dlPFC, vmPFC, and insula in the tTIS arm but not the sham. We also hypothesize that changes in the resting-state FC will be associated with changes in anatomical connectivity between the sgACC and the abovementioned brain regions. Additional exploratory analyses of changes in the whole-brain FC of the sgACC and their association with anatomical connectivity will be performed.

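### The predicted rise in sgACC BOLD power and CBF is not reconciled with the protocol's own account of hyperactivity and treatment-related decrease, and the protocol does not say how a fall would be read

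*Protocol article*

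**What the plan says.** Section 2 (Objectives and hypotheses) gives the primary aim as showing engagement of the sgACC, superior to sham. Its measure of engagement has no direction: "Target engagement will be measured as pre- vs. post-treatment change in" BOLD activity, CBF, and both of these in connected networks. BOLD activity is "quantified by power in the BOLD characteristic frequency range (0.015–0.08 Hz").

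The specific hypotheses do have a direction. Hypothesis (a) is "an increase in BOLD activity in sgACC voxels in tTIS arms but not the sham due to the direct stimulation of the area". Hypothesis (b) is "an increase in CBF in sgACC voxels in tTIS arm but not the sham", with the same reason. Section 3.12.1 repeats both under the primary outcomes: "an increase in the BOLD activation and CBF in the sgACC voxels in the tTIS arm but not the sham". It plans Wilcoxon signed-rank or paired *t*-tests of pre-post change in sgACC signal and does not state whether they are one- or two-sided.

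The background reads differently. Section 1.3 says that "functional hyperactivity of this region best characterizes more treatment-resistant patients", and among the foundations for testing tTIS it lists a "predictable decrease in the sgACC activity in response to pharmacological and somatic antidepressant treatments". Section 1.2 says that "tTIS alters the timing, but not the rate, of neuronal spiking activity", and adds that tTIS can lower synchrony in deep structures.

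**The concern.** The sign predicted for two primary measures runs against the sign that the rationale associates with antidepressant treatment, and the protocol offers no bridge between them. If sgACC CBF fell more under active stimulation than under sham, one reader could report engagement, because the measure changed and the change fits Section 1.3. Another could report that hypotheses (a) and (b) failed, because the measure did not rise. If it rose, one reader could report success and another could ask why a rise is the desired result in a region described as overactive.

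The choice between these readings would then be made after the result is known. This matters beyond wording: the Discussion makes successful engagement the condition for further work on tTIS in MDD, and Section 3.12.1 plans to regress clinical outcome on the engagement measures, where the expected sign affects interpretation.

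**Working it through.** The plan states no figure on this point, so there is none to reproduce. The check is a comparison of passages, followed by a short illustration.

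**1. Predicted direction and its reason.** Sections 2 and 3.12.1 agree with each other: BOLD power and CBF go up in the active arm and not in sham. Section 2 gives direct stimulation as the reason; Section 3.12.1 adds none.

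**2. What the rest of the protocol implies for each measure.**

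| Source | Content | Bearing on CBF | Bearing on BOLD power, 0.015–0.08 Hz |
|---|---|---|---|
| 1.2 | Spike timing changes, rate does not; synchrony can fall | No basis for a rise | Does not fix a sign |
| 1.3 | Hyperactivity in more treatment-resistant patients | A rise would move away from normal in such patients | Same, if power tracks activity |
| 1.3 | Activity falls with antidepressant treatments | Points to a fall if tTIS acts like them | Weaker, since power is a fluctuation measure |
| Discussion | Resting-state BOLD change may be small | Not addressed | Concerns size, not sign |

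**3. Comparison with hypothesis (c).** The predicted rise in functional connectivity has its own reason in Section 2: the chosen nodes show reduced connectivity in unmedicated MDD, so a rise moves them toward healthy controls. Hypotheses (a) and (b) have no corresponding argument. Hypothesis (d) concerns an association and does not depend on the BOLD or CBF sign.

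**4. Criterion against prediction.** Engagement is change (Section 2) and the stated tests are tests of change (Section 3.12.1). A significant fall would satisfy the first and contradict the prediction. Nothing says which governs. In addition, a rise in one arm but not the other, judged from pre-post tests, is not a comparison of the arms, although the lead hypothesis claims superiority to sham.

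**5. Illustration.** The documents give no expected effect on these measures, so the true standardized effects *d* below are assumptions.

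- Between arms, *n* per arm: noncentral *t* with df = 2*n* − 2 and noncentrality *d*√(*n*/2). For *n* = 15: df = 28, critical value 2.048, noncentrality −0.5 × √7.5 = −1.37 or −0.8 × √7.5 = −2.19.
- Active arm only, paired: df = *n* − 1 = 14, noncentrality *d*√15, with *d* in SDs of the change.
- Two-sided 5% throughout.

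| Assumed *d* | Between arms: significant rise | Between arms: significant fall | Active arm paired: significant rise | Active arm paired: significant fall |
|---|---|---|---|---|
| 0 | 0.025 | 0.025 | 0.025 | 0.025 |
| −0.25 | 0.0044 | 0.097 | 0.0021 | 0.145 |
| −0.5 | 0.0005 | 0.262 | 0.0001 | 0.438 |
| −0.8 | 0.00002 | 0.562 | <0.0001 | 0.821 |

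With the planned 15% dropout, 15 × 0.85 = 12.75, or about 13 per arm. The between-arm chance of showing the fall is then 0.231 at *d* = −0.5 and 0.499 at *d* = −0.8.

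**The case against.** The strongest reply is that a prediction is not a criterion. Engagement is measured as change, no one-sided test is stated, and the connectivity criterion is any significant change. A fall would therefore be seen. The planned regressions on clinical outcome and on individual electric field strength do not depend on a sign either. This stands, and it limits the point to interpretation.

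The reply can go further, and most of it also stands:

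- Section 1.3 puts altering connectivity ahead of normalizing absolute sgACC activity, and the treatment-related decrease is only one of several grounds listed.
- The decrease is reported for other treatments. No section says that tTIS lowers CBF or BOLD power.
- Hyperactivity is tied to more treatment-resistant patients, and Section 3.2 does not require resistance. Other evidence cited for hyperactivity comes from provoked mood or emotional tasks, while this trial scans at rest.
- Spike rate does not determine slow BOLD power.
- A pilot may state a falsifiable directional hypothesis, and a direct effect of stimulation could differ in sign from a therapeutic one.

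These points weaken any certainty of a fall, but none supports a rise. The protocol does not itself argue that direct and therapeutic effects differ in sign, and its post-treatment scan comes at Visit 10, the end of the course, when clinical outcome is also assessed.

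A reader might infer that an effective treatment would fail the trial's primary hypotheses, or that the trial could not tell whether the target was engaged. The documents do not support either: only (a) and (b) are involved, and change in either direction fits the stated measure of engagement.

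**Conclusion.** The point holds as an unreconciled direction, not as a defect that would hide an effect. Hypotheses (a) and (b) predict a rise justified only by direct stimulation, while the protocol's own background describes hyperactivity and a fall with antidepressant treatments. The status of a fall as engagement or as a failed hypothesis is left open. The conflict is clearest for CBF and arguable for BOLD power; (c) and (d) are not affected.

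The point has no numerical size of its own. The probabilities above follow from an assumed fall of up to 0.8 SD. They show only that, if the sgACC responded in that way, (a) and (b) would almost never be confirmed while a two-sided contrast could still detect the change. They do not show that a fall is the likelier outcome.

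**What to change.** For sgACC BOLD power and CBF, define engagement as a two-sided active-versus-sham difference, either in the post-treatment value adjusted for baseline or in the change from baseline. This replaces a rise in active but not in sham judged from pre-post paired tests.

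Then either justify the predicted rise against Sections 1.2 and 1.3 or drop it. State before unblinding how a rise and a fall will each be interpreted, including the sign expected in the regressions on clinical outcome. Align Section 2 with both the hypotheses and the test description in Section 3.12.1.

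The cost is wording in the protocol and analysis plan, with no added participants, scans or data. The downside is that the directional prediction is given up if it cannot be justified.
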